### 2.2.2 Secondary endpoints

- To evaluate the pharmacokinetic parameters of IBI362 in patients with type 2 diabetes, including but not limited to: time to maximum concentration ( $T_{max}$ ), maximum concentration ( $C_{max}$ ), area under the curve (AUC), volume of distribution (Vd), half-life ( $T_{1/2}$ ), clearance (CL), accumulation ratio (AR), etc.;
- To assess the pharmacodynamics parameters of IBI362 after multiple doses: changes of fasting blood glucose, glucagon, insulin, fasting C-peptide, hemoglobin A1c (HbA1c), oxytomodulin (OXM) and GLP-1 after administration;
- Changes of fasting blood glucose, insulin and glucagon at steady state in each dose level during dose escalation;
- Changes from baseline in each parameter of MTT test after multiple dose administration;
- Changes of self-measure blood glucose after multiple doses;
- The incidence of anti-IBI362 antibody (ADA) and neutralizing antibody (NAb) in serum before and after administration

### 2.2.3 Exploratory Endpoints

- To evaluate the effect of IBI362 on weight loss (changes in fasting body weight, waist circumference and BMI);
- To assess the improvement of the pancreatic function: changes in homeostatic model assessment (HOMA) of  $\beta$ -cell function and insulin resistance (IR).

## 3 Overall Study Design

### 3.1 Design Rationale

This study will be the first to evaluate the safety, tolerability and PK/PD of IBI362 administered as multiple injections in Chinese patients with type 2 diabetes. A multicenter, randomized double-blind, placebo-controlled trial design will be used, while dulaglutide is set as an open-label active control.

#### 3.1.1 Dose Selection Principle

IBI362 is proposed to be studied for the tolerability of 3 dosing regimens (1 mg QW4 + 2 mg QW4 + 3 mg QW4; 1.5 mg QW4 + 3 mg QW4 + 4.5 mg QW4; 2 mg QW4 + 4 mg QW4 + 6 mg QW4) in Chinese patients. The dose selection and interval design for

this tolerability study will be primarily based on the following considerations:

1) Safe Induction Dose

[REDACTED]  
[REDACTED]  
[REDACTED]  
[REDACTED]  
[REDACTED]. The proposed induction doses of 1 mg and 1.5 mg QW4 are the validated safe dose range. The 2-mg serial dosing regimen will be initiated 4 weeks after the start of the 1.5-mg serial dosing regimen with acceptable safety.

2) Inducible Tolerance Potential

[REDACTED]  
[REDACTED]  
[REDACTED]  
[REDACTED]  
[REDACTED]  
[REDACTED]  
[REDACTED]

3) Mature safety monitoring methods and slow climbing speed

The major adverse effects of OXM-3 targets arise from gastrointestinal reactions and are easily monitored. Both 1.0 mg and 1.5 mg are verified safe doses. The increase is 33.3% in the 2.0-mg dose group compared with previous dose group, and the rate of increase is slow.

4) Potential for better therapeutic benefit

[REDACTED]  
[REDACTED]  
[REDACTED]  
[REDACTED]  
[REDACTED]  
[REDACTED]  
[REDACTED]  
[REDACTED]

5) [REDACTED]  
[REDACTED]  
[REDACTED]  
[REDACTED]  
[REDACTED]  
[REDACTED]  
[REDACTED]  
[REDACTED]

## 3.2 Phase 1b/2 Study Design

### 3.2.1 Overall Study Design

The study will be planned to include 42 patients with type 2 diabetes who failed to control HbA1c after at least 2 months of lifestyle intervention or stable dose of metformin ( $\geq 1000$  mg/day or maximum tolerated dose). The study will be divided into three cohorts, which will be Cohort 1 (n = 14), Cohort 2 (n = 14) and Cohort 3 (n = 14). Patients in each cohort will be randomized 8:4:2 to IBI362 group (n = 8), placebo group (n = 4), or dulaglutide 1.5 mg group (n = 2). The active control, dulaglutide, will be administered as 1.5 mg once-weekly for 12 weeks in Cohorts 1, 2 and 3, and the dosing schedules for IBI362 and placebo are described below:

**Cohort 1:** Patients randomized to IBI362 or placebo initiate treatment with 1.0 mg once-weekly with dose escalations every 4 weeks by 1 mg until the maintenance dose (3.0 mg) will be achieved.

**Cohort 2:** Patients randomized to IBI362 or placebo initiate treatment with 1.5 mg once-weekly with dose escalations every 4 weeks by 1.5 mg until the maintenance dose (4.5 mg) will be achieved.

If the patient failed tolerate 3.0 mg or 4.5 mg with the met discontinuation criteria, the patient needs to explore the next dose according to Cohort 2 (backup 1) or Cohort 2 (backup 2).

**Cohort 2 (backup 1):** With the tolerated dose of 3.0 mg, the dose should be reduced to 2.25 mg after 1-week break and treat with it for 2 weeks. After that, if it is well-tolerated, the dose will be increased to 3.0 mg and treat for 4 weeks.

**Cohort 2 (backup 2):** If the dose of 4.5 mg is intolerable to the patient, the dose should be reduced to 3.75 mg after 1-week break and administered continuously for 2 weeks till the end of the trial.

**Cohort 3:** Dosing should not be started until the patients in Cohort 2 complete the 4-week tolerability evaluation of 1.5 mg. If 1.5 mg is not well-tolerated, 2.0 mg and higher doses in Cohort 3 will not be explored. Patients randomized to IBI362 or placebo initiate treatment with 2.0 mg once-weekly with dose escalations every 4 weeks by 2.0 mg until the maintenance dose (6.0 mg) will be achieved.

The study will consist of a 3-week screening period, a 12-week double-blind treatment period, and an 8-week follow-up period.

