|                           | 
Cohort 2: Patients randomized to IBI362 or placebo initiate treatment with 1.5 mg once-weekly with dose escalations every 4 weeks by 1.5 mg until the maintenance dose (4.5 mg) will be achieved.
 
If 3.0 mg or 4.5 mg is not tolerated in Cohort 2, the dose should be adjusted according to the criteria in Table 1.
 
Cohort 3: Dosing should not be started until the patients in Cohort 2 complete the 4-week tolerability evaluation of 1.5 mg. If 1.5 mg is not well-tolerated, 2.0 mg and higher doses in Cohort 3 will not be explored. Patients randomized to IBI362 or placebo initiate treatment with 2.0 mg once-weekly with dose escalations every 4 weeks by 2.0 mg until the maintenance dose (6.0 mg) will be achieved.
 
The study will consist of a 3-week screening period, a 12-week double-blind treatment period, and an 8-week follow-up period.
 
Discontinuation Criteria: If any of the following criteria are met, the investigator and the sponsor should immediately initiate a discussion to decide whether to terminate dose escalation.
 
 
• Occurrence of at least one serious treatment-emergent adverse event related to IBI362 (except for expected adverse events related to the pharmacological properties of IBI362, such as hypoglycemia, etc.).
 
• No less than 4 patients experience symptomatic hypoglycemic events (plasma glucose levels < 3.0 mmol/L) at a specific dose level, and those events are considered to be related to IBI362.
 
• No less than 2 patients receiving IBI362 experience persistent (more than one week) symptoms of acute pancreatitis.
 
• No less than 2 patients experience severe IBI362-related, non-serious adverse events at the same dose, regardless of whether the event is associated with the same organ or system.
 
 |

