**Notes:**

\* If patients in Cohort 2 cannot tolerate 3.0 mg during dose escalation, the dose should be reduced to 2.25 mg after 1-week break in Cohort 2 (backup1), and subsequent dose escalation should be performed as Cohort 2 (backup1);

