**Intolerance criteria for a single patient:**

1. If venous plasma glucose < 3.0 mmol/L or venous plasma glucose does not reach the criteria of < 3.0 mmol/L, but the symptoms of hypoglycemia are obvious and cannot be resolved spontaneously, repeated measurement of blood glucose is required before the next dose. If the criteria are still met, the patient is considered to be intolerant at this dose;
2. Other severe intolerance considered by the investigator to be related to the study drug occurred, and the investigator consider it necessary to stop the trial after discussion with the sponsor, and at this case the patient is considered to be intolerable at this dose.

Table 2. Schedule of Activities

| Stage                                                                          | Screening Period  | Baseline | Treatment Period  |   |   |   |   |   |    |    |    |    |        |    |    |    |    |        |    |    |        |    | Safety Follow-up | Early Termination |     |
|--------------------------------------------------------------------------------|-------------------------------|----------|-------------------------------|---|---|---|---|---|----|----|----|----|--------|----|----|----|----|--------|----|----|--------|----|------------------|-------------------|-----|
| Study duration (days)                                                          | - 21 to -2                    | - 1      | 1                             | 2 | 3 | 4 | 5 | 6 | 8  | 15 | 22 | 24 | 29     | 36 | 43 | 50 | 52 | 57     | 64 | 71 | 78     | 80 | 85               |                   | 134 |
| Study duration (weeks)                                                         | - 3 to - 1                    | - 1      | 1                             |   |   |   |   |   | 2  | 3  | 4  |    | 5      | 6  | 7  | 8  |    | 9      | 10 | 11 | 12     |    | 13               |                   | 20  |
| Window (days)                                                                  | /                             |          | /                             | / | / | / | / | / | ±2 | ±2 | ±2 | /  | ±2     | ±2 | ±2 | ±2 | /  | ±2     | ±2 | ±2 | ±2     | /  | ±2               |                   | ±3  |

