3. Standard meal test (MTT) collection measures included: insulin, C-peptide, plasma glucose, glucagon, endogenous OXM, and endogenous GLP-1. The sampling points include: fasting, 30 min, 1h, 2h, 3h and 4h. A total of 9 mL blood will be collected from each blood collection point. See the manual of the central laboratory for the detailed operation process. Fasting state refers to fasting for 10 hours. [ The standard meal is instant noodles. The master Kang roast beef noodles (bucket noodles) purchased by the sponsor in a unified manner are removed from the oil bag. The noodles are soaked in boiled water and then removed. The seasoning bag is added and mixed well. The time is counted from the first bite of eating. The noodles are eaten within 10 minutes, and 200 mL of water is drunk; or the instant noodles are directly opened with 200 mL of boiled water to ensure that the noodles are eaten and the water or soup is drunk]. Visit days when MTT test is performed: 1 day prior to Cycle 1 administration, Day 80 (D80).
4. If the patient experiences drug-related adverse events during dose escalation and meets the protocol-specified tolerance criteria, dose adjustment is required at the investigator's discretion, and a standard meal test should be performed 48 hours after the first dose after dose adjustment.
- Test by central laboratory

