### 3.2.3 Discontinuation Criteria

**If any of the following criteria are met, the investigator and the sponsor should immediately initiate a discussion procedure to decide whether to terminate the dose escalation in each cohort.**

- Occurrence of at least one serious treatment-emergent adverse event related to IBI362 (except for expected adverse events related to the pharmacological properties of IBI362, such as hypoglycemia, etc.).
- No less than 4 patients experience symptomatic hypoglycemic events (plasma glucose levels < 3.0 mmol/L) at a specific dose level, and those events are considered to be related to IBI362.
- No less than 2 patients receiving IBI362 experience persistent (more than one week) symptoms of acute pancreatitis.
- No less than 2 patients experience severe IBI362-related, non-serious adverse events at the same dose, regardless of whether the event is associated with the same organ or system.

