### **2.2 STUDY DESIGN**

The study was planned to include 42 patients with type 2 diabetes who failed to achieve HbA1c control after at least 2 months of lifestyle intervention or stable dose of metformin ( $\geq 1000$  mg/day or maximum tolerated dose). The study was divided into three cohorts, which were Cohort 1 (n = 14), Cohort 2 (n = 14), and Cohort 3 (n = 14), and patients in each cohort were randomly divided into IBI362 treatment group (n = 8), placebo group (n = 4), and dulaglutide 1.5 mg treatment group (n = 2) in an 8:4: 2 ratio. The active comparator drug, dulaglutide, was administered at 1.5 mg QW for 12 weeks in Cohorts 1, 2, and 3, and the dosing schedules for IBI362 and placebo are described below:

Cohort 1: The initial dose is 1.0 mg once weekly for 4 weeks. If well tolerated, the dose should be increased to 2.0 mg once weekly. After 4 weeks of treatment, the subject's tolerance should be evaluated again. If well tolerated, the dose should be increased to 3.0 mg once weekly for 4 weeks (escalation by 1 mg every 4 weeks to the target dose).

Cohort 2: The initial dose of the subject is 1.5 mg, once weekly for 4 weeks. If well tolerated, the dose will be increased to 3.0 mg, once weekly for 4 weeks. After that, the subject's tolerance will be evaluated again. If 3.0 mg cannot be tolerated according to the intolerance criteria, the subject need to initiate the next dose according to Cohort 2 (backup 1); if 3.0 mg is well tolerated, the dose will be increased to 4.5 mg, once weekly for 4 weeks. If 4.5 mg can not be tolerated according to the intolerance criteria, the subject need to initiate the next dose according to Cohort 2 (backup 2) (escalation by 1.5 mg every 4 weeks to the target dose).

Cohort 2 (backup 1): If 3.0 mg cannot be tolerated, the dose should be reduced to 2.25 mg after 1-week break and continued to be increased to 3.0 mg after 2-week treatment. If well tolerated, the dose should be increased to 3.0 mg and administered for 4 weeks.

Cohort 2 (backup 2): If 4.5 mg cannot be tolerated, the dose should be reduced to 3.75 mg after 1-week break and administered for 2 weeks till the end of the trial.

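### The primary safety endpoint is defined per dose level, but the SAP tabulates adverse events only by cohort; the Cohort 2 step-down wording in protocol 3.2.1 also needs a small correction

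*Combined protocol and SAP*

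**What the plan says.** **Endpoint.** Protocol 2.2.1 makes the primary safety endpoint the frequency and severity of adverse events per dose level while the dose is being escalated. SAP 3.1 keeps that definition. Protocol 7.1 speaks of dose stages for the same measure.

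**Tables.** SAP 6.6.1 summarises adverse events by treatment group and by system organ class, preferred term and severity. SAP 6.1 sets the IBI362 treatment groups as Cohorts 1, 2 and 3 and makes the group size the default denominator. Protocol 9.4.3 likewise summarises by arm. The table of changes in SAP 2.5.2 says nothing about dose level.

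**Step-down in Cohort 2.** Protocol 3.2.1 says "If the patient failed tolerate 3.0 mg or 4.5 mg with the met discontinuation criteria, the patient needs to explore the next dose" and then points to the two backup schedules. Its backup 1 paragraph begins "With the tolerated dose of 3.0 mg, the dose should be reduced to 2.25 mg after 1-week break". Elsewhere the trigger is patient-level intolerance. The synopsis says "If 3.0 mg or 4.5 mg is not tolerated in Cohort 2, the dose should be adjusted according to the criteria in Table 1", the note to Table 1 says "If patients in Cohort 2 cannot tolerate 3.0 mg during dose escalation, the dose should be reduced to 2.25 mg after 1-week break", and SAP 2.2 says "If 3.0 mg cannot be tolerated according to the intolerance criteria, the subject need to initiate the next dose". The second of the single-patient criteria under Table 1 applies to severe related intolerance "and the investigator consider it necessary to stop the trial after discussion with the sponsor". Yet note 4 to Table 3 says that, for a patient who has a drug-related event and "meets the protocol-specified tolerance criteria, dose adjustment is required at the" investigator's discretion.

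**The concern.** The study is meant to determine a safe dose range, and its rules work by dose level. The maximum tolerated dose is the level before the one at which escalation stopped. One of the stopping criteria in protocol 3.2.3 reads "No less than 2 patients experience severe IBI362-related, non-serious adverse events at the same dose", and the hypoglycemia criterion also counts patients at one level. A column that pools a patient's starting, middle and top doses cannot show at which of them an event began. If only the planned tables are produced, the primary safety endpoint as defined is not reported, and no document records a decision to drop it.

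The step-down wording raises a smaller issue. The only section headed as discontinuation criteria is 3.2.3, which is for deciding whether a cohort's escalation should end. Three of its four criteria need 2 or 4 patients, so they do not suit a decision about one patient's next dose. The backup 1 sentence says the reverse of what the Table 1 note says, and single-patient criterion 2 speaks of stopping where the consequence is adjustment.

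**Working it through.** **1. Planned size.** Three cohorts of 8 + 4 + 2 give 3 × 14 = 42, which agrees with protocol 9.2. There is no power calculation to reproduce.

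**2. Dose levels against table columns.** From the synopsis dosing schedules, with 8 IBI362 patients per cohort:

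| SAP column | Weeks 1–4 | Weeks 5–8 | Weeks 9–12 |
|---|---|---|---|
| Cohort 1 | 1.0 mg | 2.0 mg | 3.0 mg |
| Cohort 2 | 1.5 mg | 3.0 mg | 4.5 mg |
| Cohort 3 | 2.0 mg | 4.0 mg | 6.0 mg |

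That is 3 × 3 = 9 cohort-by-level cells in 3 columns. There are 7 distinct planned levels. If everyone escalates, 2.0 mg and 3.0 mg are each given to 8 + 8 = 16 patients, and the other five levels to 8 each. The Cohort 2 backups would add 2.25 and 3.75 mg. No planned column isolates a level.

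**3. Could dose level mean cohort?** The endpoint in 2.2.1 is tied to the escalation period, 7.1 calls the units stages, and SAP 3.4 uses dose phases within escalation for glucose and insulin. These point to the level being taken, not the cohort's target dose.

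**4. Does anything else in the SAP supply the split?** SAP 6.6 groups by treatment actually received, but the groups remain those of 6.1. SAP 5.3 allows an event's cycle number to be marked if needed, but no listed table uses it.

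**5. What the layout hides.** Table S3 has the cohort layout. Its 6.0 mg column covers the planned weeks on 2.0, 4.0 and 6.0 mg, and reports gastrointestinal disorders in 4 of 8 patients. The number with an onset on 6.0 mg is therefore somewhere between 0 and 4. If all 8 received 6.0 mg, the dose-level incidence lies between these two cases (Clopper-Pearson 95% intervals):

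- 0/8 = 0%, interval 0 to 36.9%
- 4/8 = 50%, interval 15.7 to 84.3%

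That all 8 reached 6.0 mg is an assumption. Fig. S5 gives n = 8 for the week-12 meal test, which is consistent with it but does not prove it.

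**6. Missing start dates.** Unless other data contradict it, SAP 5.3 moves an onset to the first dose in three situations: the date is wholly missing; only the year is known and it is the year of first dose; or the month is known and it is the month of first dose. Otherwise it uses 1 July or day 15. These rules serve durations, but in a dose-level table the first two would assign events to the starting dose without evidence, and the mid-month or mid-year defaults could also pick the wrong level.

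**7. The step-down wording.** Of the places that state the Cohort 2 rule, the synopsis, the Table 1 notes and SAP 2.2 agree on patient-level intolerance, and 3.2.1 differs. The list in protocol 4.4.1 is patient-level too, but it concerns stopping study drug, so it does not fit a step-down either.

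**The case against.** The best defence of the tables is that nothing is lost. All adverse events and all exposure are to be listed, the levels are fixed four-week blocks, and the dose at onset can be derived. With at most 8 IBI362 patients per cell, and level tied to time on drug, the rates would be descriptive and could not separate a dose effect from time on treatment. All of this stands. It limits what the table can show, but it does not excuse leaving out the table that the endpoint definition calls for.

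A reader might also infer that the maximum tolerated dose is unsupported. The documents do not say that: it follows from the decision under 3.2.3, and a dose-level table would only document it.

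On the step-down, a reader might infer that under 3.2.1 a lone patient with a severe related event would be refused a lower dose until a second patient was affected. The text does not support this. The sentence cites no section number and its subject is one patient. The backup 2 paragraph of the same section turns on the dose being intolerable to that patient, and a cut to 2.25 mg makes sense only if 3.0 mg was not tolerated. Nor does criterion 2 set 3.2.1 against the synopsis and the SAP, since for severe events other than hypoglycemia they rely on that same criterion.

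A reader might further infer that Cohorts 1 and 3 have no provision for intolerance. The notes to Table 2, note 4 to Table 3 and protocol 4.4.2 (for gastrointestinal reactions) provide for adjustment without limiting it to Cohort 2. What is missing is a named reduced dose, which is a matter of detail.

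**Conclusion.** The main point holds and should be corrected. The plan defines its primary safety endpoint by dose level and specifies no adverse event table by dose level. Nine cells become three columns, and for a result such as 4 of 8 in the 6.0 mg column the incidence attributable to onset on 6.0 mg is unknown between 0% and 50% (if all 8 received that dose). The conclusion rests on reading dose level as the dose being taken, which protocol 7.1 and SAP 3.4 support. It is a gap in specification and reporting. It changes no figure stated in the plan and does not show that any reported count is wrong.

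The 3.2.1 wording is a real but minor inconsistency, to be corrected for agreement with the rest of the documents. No effect on patient handling, discontinuations or the maximum tolerated dose can be shown from the text.

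**What to change.** **SAP 6.6.1.** Add treatment-emergent adverse event incidence and severity by cohort and dose level at onset.

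- Denominator: patients who received at least one dose at that level, as a stated exception to the default in SAP 6.1.
- Onset after the last dose goes to the last level received.
- Show placebo and dulaglutide by the same periods: weeks 1–4, 5–8 and 9–12.
- Where the recorded start date, wholly or partly missing, does not determine the level, show the event as level unknown. Do not use the SAP 5.3 imputation to the first dose for this purpose.
- State that the rates are descriptive and confounded with time on drug.

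**Protocol wording.** In 3.2.1, replace the reference to discontinuation criteria in the Cohort 2 sentence by the single-patient intolerance criteria under Table 1. Open backup 1 with 3.0 mg not being tolerated. In single-patient criterion 2, replace the need to stop the trial by inability to continue at this dose.

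**Cost.** One derived variable from data already listed, extra tables with small counts, and a few words of protocol text. No added patients, visits or samples.

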### 2.2 Study Endpoints

#### 2.2.1 Primary endpoint

- **Safety and tolerability:** During dose escalation, the incidence and severity of adverse events at each dose level, including chief complaint, physical examination, laboratory tests (hematology, blood chemistry, lipid panel, coagulation function, urinalysis, myocardial enzymes, serum amylase and/or lipase, thyroid function, calcitonin, etc.), vital signs (pulse, respiration, blood pressure, body temperature), 12-lead ECG and other examinations; treatment compliance; and record the name, clinical characteristics, severity, start and stop time, supportive care and outcomes of adverse events, correlation with the study drugs;

- **Maximum tolerated dose:** If the dose exploration is stopped when the criteria for stopping dose escalation are met at a certain dose level, the previous dose is the maximum tolerated dose. If the criteria are still not met when the maximum exploratory dose is reached, the maximum tolerated dose is greater than or equal to the maximum escalation dose.

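### Protocol 3.2.1 moves Cohort 2 patients to a backup schedule on the discontinuation criteria (and, for backup 1, on a tolerated dose), whereas the synopsis, Table 1 and SAP 2.2 use patient-level intolerance

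*Combined protocol and SAP*

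**What the plan says.** Cohort 2 escalates from 1.5 to 3.0 to 4.5 mg, with two backup schedules for patients who do not manage 3.0 mg (backup 1) or 4.5 mg (backup 2).

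Protocol 3.2.1 gives the entry rule as "If the patient failed tolerate 3.0 mg or 4.5 mg with the met discontinuation criteria, the patient needs to explore the next dose", followed by a reference to the two backups. It then opens backup 1 with "With the tolerated dose of 3.0 mg, the dose should be reduced to 2.25 mg after 1-week break" and backup 2 with "If the dose of 4.5 mg is intolerable to the patient, the dose should be reduced to 3.75 mg".

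The Table 1 note for backup 1 reads "If patients in Cohort 2 cannot tolerate 3.0 mg during dose escalation, the dose should be reduced to 2.25 mg". Directly after the notes comes a list of intolerance criteria that is expressly for a single patient. SAP 2.2 reads "If 3.0 mg cannot be tolerated according to the intolerance criteria, the subject need to initiate the next dose". The synopsis sends the reader to the criteria in Table 1. Note 4 to Table 3 speaks of meeting the tolerance criteria, with adjustment at the investigator's discretion.

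Protocol 3.2.3, the section headed Discontinuation Criteria, says that when any criterion is met the investigator and sponsor should "immediately initiate a discussion procedure to decide whether to terminate the dose escalation in each cohort". Its criteria are at least one related serious event, at least 4 patients with related symptomatic hypoglycemia at a dose level, at least 2 with persistent pancreatitis symptoms, or at least 2 with severe related non-serious events at the same dose.

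**The concern.** Section 3.2.1 is the main design section of the protocol, and its step-down rule does not match the other statements of the same rule. Two phrases are at fault. The first names a set of criteria whose matching heading belongs to a dose-level list with a different purpose. The second conditions backup 1 on the opposite of what Table 1 and the SAP require.

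A site that follows Table 1 can step down one intolerant patient. A site that follows 3.2.1 literally would wait until the dose-level criteria are met, or would be told to reduce the dose of someone who tolerates it.

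The trigger bears on the data as well as the conduct. The primary endpoint in 2.2.1 is the incidence and severity of adverse events at each dose level, so who stays at 3.0 or 4.5 mg affects what is counted there. It also affects relative dose intensity (SAP 6.4.1) and who has the extra meal test after a dose adjustment (Table 3 note 4).

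**Working it through.** **1. The rule as stated in each place**

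| Place | Condition for moving to a backup schedule |
|---|---|
| Synopsis, Study design | 3.0 or 4.5 mg not tolerated; refers to Table 1 |
| Protocol 3.2.1, Cohort 2 | not tolerated and discontinuation criteria met |
| Protocol 3.2.1, backup 1 | 3.0 mg tolerated |
| Protocol 3.2.1, backup 2 | 4.5 mg intolerable to the patient |
| Table 1 notes | 3.0 mg (backup 1) or 4.5 mg (backup 2) cannot be tolerated |
| List under Table 1 | intolerance, defined for one patient |
| Table 3 note 4 | tolerance criteria met; investigator's discretion |
| SAP 2.2 | intolerance criteria, applied to the subject |

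The two outliers are both in 3.2.1.

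**2. Could the phrase point elsewhere?** Section 3.2.1 gives no cross-reference. The other candidate is 4.4.1, Treatment discontinuation. It governs stopping study drug, and under 4.4.3 permanent discontinuation leads to withdrawal. Neither 3.2.3 nor 4.4.1 describes a reduced dose, so neither reading yields the backup schedules.

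**3. Are the two triggers equivalent?** Plasma glucose below 3.0 mmol/L appears in both lists. Under the single-patient criteria, one patient qualifies if the finding is confirmed before the next dose. Under 3.2.3 at least 4 patients are needed at a dose level, with symptoms and a judged relation to IBI362. For severe related non-serious events 3.2.3 needs at least 2 patients. One related serious event is enough for 3.2.3, so the triggers can coincide.

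**4. Size, on assumed rates.** The plan has no power calculation to reproduce. Its enrolment figure does reproduce: 3 × (8 + 4 + 2) = 42. The documents give no intolerance rate, so p is assumed over a range. The simplification is that the same event counts under both rules and patients are independent. With n = 8 on IBI362 in a cohort:

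- P(at least one) = 1 − (1 − p)^8
- P(exactly one) = 8p(1 − p)^7, the case that is met per patient but misses a 2-patient rule
- P(one to three) = P(at least one) − P(at least four), the case that is met per patient but misses the 4-patient rule

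| Assumed p | At least one | At least two | At least four | Exactly one | One to three |
|---|---|---|---|---|---|
| 5% | 0.337 | 0.057 | <0.001 | 0.279 | 0.336 |
| 10% | 0.570 | 0.187 | 0.005 | 0.383 | 0.565 |
| 25% | 0.900 | 0.633 | 0.114 | 0.267 | 0.786 |
| 40% | 0.983 | 0.894 | 0.406 | 0.090 | 0.577 |

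For example, at 10%: 8 × 0.10 × 0.90^7 = 0.8 × 0.4783 = 0.383.

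**The case against.** The best defence is that the intended rule can be recovered. The sentence in 3.2.1 is about one patient, backup 2 in the same section speaks of the patient, and the synopsis, Table 1, Table 3 and the SAP all use intolerance. The word tolerated in backup 1 follows a sentence about failing to tolerate the dose. Read literally, it would contradict the Cohort 2 schedule in the same section, so it is almost certainly a language slip. Most of this stands. It makes the fault one of wording. It does not make 3.2.1 harmless, because an instruction that has to be corrected from other pages can be followed as written.

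It is also fair that 4.4.1 does not strictly exclude a step-down: for laboratory findings, stopping is to be considered after discussion, and 4.4.2 suggests adjusting titration first for gastrointestinal reactions. That weakens any claim of direct conflict with 4.4.1, but 4.4.1 still does not supply a step-down trigger.

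The probabilities are illustrations only. The single-patient criteria and the 3.2.3 criteria do not count the same events, and the chance of exactly one affected patient rises and then falls with the rate. No single percentage describes how often the readings would diverge.

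A reader might go further and infer that the maximum tolerated dose depends on which page is read, or that backup 1 gives again a dose already scored as above it. The documents do not support either. The rule that "the previous dose is the maximum tolerated dose" has the same wording in the synopsis, 2.2.1, 7.1 and SAP 3.1. It applies when exploration is stopped under the stopping criteria, and single-patient intolerance does not enter it. Meeting 3.2.3 only opens a discussion and does not by itself place any dose above the maximum tolerated dose.

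**Conclusion.** The contradiction holds, and it is confined to two phrases in protocol 3.2.1: the trigger named there, and the backup 1 condition. Taken literally they change who steps down in Cohort 2, and through that the exposure and the adverse events recorded at 3.0 and 4.5 mg. The conclusion rests on the text alone and needs no assumed rate.

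The size cannot be fixed from the documents. Under the simplification above, the per-patient trigger would be met while a 2-patient criterion is not in about 28%, 38%, 27% and 9% of cohorts at rates of 5%, 10%, 25% and 40%. One related serious event would close that gap. SAP 6.1 defines its table groups by cohort, so a step-down does not move a patient into another cohort's group. This is a wording fault in an operative dosing rule and should be corrected.

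**What to change.** Reconcile the two phrases in 3.2.1 with the synopsis, Table 1 and its single-patient criteria, and SAP 2.2:

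- Name one set of criteria as the trigger for the backup schedules, with a section or table reference, and state whether it is applied per patient or per cohort. Use that name in every place.
- Reword the opening of backup 1 in 3.2.1 so that it no longer contradicts Table 1 and SAP 2.2.

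Which rule applies is for the sponsor and investigators. The cost is a wording amendment to 3.2.1. If the trigger chosen is not the one Table 1 and SAP 2.2 already share, those places need a matching edit. No extra data are required, and neither the sample size nor the analysis changes.
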